### C. Description of study design

**C.1. Trial Design:** Two-wave randomized controlled online survey experiment.

**C.2. Study Setting / Recruitment / Randomization / Blinding / Data collection**

We will recruit participants from the KnowledgePanel, which is a nationally representative online survey panel maintained by a survey research company Ipsos. KnowledgePanel is a largest probability-based online panel consisting of about 55,000 adult members that covers 97% of the U.S. adult population. KnowledgePanel includes good representation of older women across the spectrum of different health status. Panel members are randomly recruited by random digit dialing telephone (until 2009) or by address (since 2009); the sampling frame includes both listed and unlisted numbers and households are provided with access to internet and hardware if needed. Extensive analyses by independent researchers have consistently found the KnowledgePanel to closely match other nationally representative surveys such as the Health and Retirement Study. KnowledgePanel has been used in numerous medical research studies involving older adults, including our own prior work. Based on prior experience we expect a response rates of 65-70% among older adults who are invited to participate.

KnowledgePanel will be responsible for inviting panel members to the study via email and for programming the survey for online administration. During the survey programming, randomization will be achieved using randomly generated numbers. To ensure matched participant characteristics across groups, participants will be sorted by the randomly generated numbers and by race/ethnicity, geographic region, education (these information have already been collected by KnowledgePanel about its members), then the participants, thus sorted, will be allocated sequentially to each of the 6 experimental groups. Participants and the research team will be blinded to the allocation until data collection is complete. Only de-identified data will be sent from KnowledgePanel to the study team.

KnowledgePanel will pretest each wave of the survey with individuals not included in the study to ensure programming and randomization procedures occur as intended. Specifically, KnowledgePanel will pretest wave 1 survey with 50 eligible older women, and pretest wave 2 survey with the same individuals, recognizing that not all 50 may complete wave 2's pretest.

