#### **C.6. Statistical methods and sample size.**

The main analysis focuses on the primary outcome assessed at Wave 2 with the independent variables being the randomly assigned message/messenger combinations. The primary goal is to compare the experimental groups (Groups 3-6) at Wave 2 with both control groups to assess the combined effect of consistent and conflicting messages over time. We hypothesize that the participants who read consistent messages both directed at reducing over-screening (Groups 3,4) will have higher support and higher intentions to stop screening than participants who read clinician message alone (Group 2); the participants who read conflicting messages (Groups 5,6) will have lower intentions to stop screening than participants who read clinician message alone (Group 2). We will compare the mean scores across groups using ANOVA and adjust for multiple comparisons. We will conduct exploratory analyses by key covariates, including age, predicted life expectancy based on health and functional status, to examine the impact of messaging within these subgroups.

Power calculations are based on preliminary data in which we asked 41 patients 65+ about willingness to stop routine cancer screening if recommended by their clinician. Based on the distribution of responses from this preliminary data, we estimate that with 400 participants randomized to each group at Wave 2, we will have 80% power to detect a 0.30 point difference for the primary outcome. The survey company Ipsos that manages and maintains the KnowledgePanel affirms that, through their recruiting strategy and based on their past experience, 20% attrition or less is expected between the two waves over 1-2 weeks. Assuming 20% attrition, we will target 500 per group at Wave 1.

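### The six groups are balanced on race/ethnicity, region and education, but the stated ANOVA omits these factors; if they lead the sort, its standard errors are slightly too large (minor)

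*Protocol*

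**What the plan says.** **Allocation (Protocol C.2).** The purpose is given as "To ensure matched participant characteristics across groups". Participants are "sorted by the randomly generated numbers and by race/ethnicity, geographic region, education" and, in that order, "will be allocated sequentially to each of the 6 experimental groups". The section adds that the panel company already holds the three factors for its members.

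**Analysis (Protocol C.6).** The main analysis concerns the primary outcome at Wave 2, "with the independent variables being the randomly assigned message/messenger combinations". The method is: "We will compare the mean scores across groups using ANOVA and adjust for multiple comparisons". Multiplicity is the only adjustment named. Covariates appear once more, in "exploratory analyses by key covariates, including age, predicted life expectancy based on health and functional status". Those are subgroup analyses, and neither named covariate is an allocation factor.

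**Power (Protocol C.6).** The calculation is made "with 400 participants randomized to each group at Wave 2". The claim for that sample size reads: "we will have 80% power to detect a 0.30 point difference for the primary outcome". No SD, alpha or sidedness is given.

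**The concern.** Sorting on three factors and dealing in turn is a stratified systematic allocation. It makes the factor mix nearly the same in every group, so differences in that mix add almost nothing to the true variability of a group contrast. An ANOVA on group alone does not take account of this. It leaves the variance explained by the factors in its residual and computes the standard error as though the groups had been formed by unrestricted randomization.

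The reported standard error is then larger than the true one. Confidence intervals are wider than they need to be, the real type I error falls below its nominal level, and some power is lost. What is at stake is calibration and a little efficiency in the comparisons of Groups 3-6 with the two controls.

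**Working it through.** **Inputs from the protocol:** 400 per group at Wave 2, a difference of 0.30 points, 80% power, 20% attrition, 500 per group at Wave 1, 3000 in total.

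**Assumptions:** two-sided 5% with no multiplicity correction for the power figures; R², the share of outcome variance explained by race/ethnicity, region and education together, of 1%, 5% or 10%.

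**1. The plan's own figures.** The Wave 1 target reproduces: 400/(1 − 0.20) = 500, and 6 × 500 = 3000. The 80% power cannot be checked without an SD, but it implies one:

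SD = 0.30 / [(1.960 + 0.842) × √(2/400)] = 0.30 / (2.802 × 0.0707) = 1.514.

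Other conventions imply other values: 1.71 for one-sided 5%, and 1.19 for two-sided 5% with Bonferroni over 8 comparisons (four experimental groups against two controls).

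**2. Excess in the standard error.** With the factors balanced by design:

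- Reported by the group-only ANOVA: SD × √(2/n) = 1.514 × 0.0707 = 0.1071.
- True: SD × √(1 − R²) × √(2/n).
- Ratio: 1/√(1 − R²). This does not depend on the SD or alpha.

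**3. Type I error and power.** Write SE for the reported value and SE* for the true one.

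- Real type I error of the group-only test: 2 × [1 − Φ(1.960/√(1 − R²))].
- Power, group only: Φ[(0.30 − 1.960 × SE)/SE*].
- Power, factors in the model: Φ[0.30/SE* − 1.960].

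| R² | SE too large by | Type I error | Power, group only | Power, with factors | 95% CI half-width, group only | 95% CI half-width, with factors |
|---|---|---|---|---|---|---|
| 1% | 0.5% | 4.9% | 80.1% | 80.4% | 0.210 | 0.209 |
| 5% | 2.6% | 4.4% | 80.6% | 82.0% | 0.210 | 0.205 |
| 10% | 5.4% | 3.9% | 81.3% | 84.0% | 0.210 | 0.199 |

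At R² = 0 the excess vanishes.

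**4. Attrition.** If a random 20% drop out, about one fifth of the factor variance returns to the group contrasts. The ratio becomes roughly 1/√(1 − 0.8 × R²), an excess of 0.4%, 2.1% or 4.3%. The table is therefore an upper figure for each R².

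**5. Simulation.** Sort-then-deal allocation was simulated with 3000 women, six groups, assumed factor distributions and 3000 runs per scenario.

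| Leading sort key | R² | Attrition | Reported SE / true SE | Type I, group only | Type I, with factors |
|---|---|---|---|---|---|
| Factors | 5% | 0 | 1.022 | 4.4% | 5.1% |
| Factors | 5% | 20% | 1.016 | 4.1% | 4.7% |
| Factors | 20% | 0 | 1.107 | 3.1% | 5.1% |
| Factors | 20% | 20% | 1.091 | 3.5% | 4.8% |
| Random number | 5% | 0 | 1.011 | 4.9% | 5.1% |
| Random number | 5% | 20% | 0.995 | 5.1% | 4.8% |
| Random number | 20% | 0 | 1.022 | 4.5% | 4.6% |
| Random number | 20% | 20% | 1.000 | 4.9% | 5.0% |

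The Monte Carlo error of a ratio is about 1/√(2 × 3000) = 1.3%. At R² = 5% the simulation alone therefore cannot separate 1.02 from 1, and the formula carries that case. At R² = 20%, a stress value above the assumed range, the excess is clear when the factors lead the sort. When the random number leads, every ratio is within simulation error of 1.

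**The case against.** **Sort order.** C.2 lists the random number first. Taken literally, an effectively unique random number as leading key leaves nothing for the factors to sort. The allocation would be simple randomization and the group-only standard error would be right. This stands as an ambiguity. The factors-first reading is the better one, because the other defeats the purpose that C.2 states, but the size of the point is conditional on it.

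**Level of detail.** C.6 is a short summary, only the protocol is at hand, and covariates are often fixed in the SAP. But C.6 is not silent: it names outcome, time point, independent variables and method, and the factors are not among them. A SAP that adds them would depart from this text.

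**Size and direction.** The R² is assumed, and the error is conservative. Both stand, and they keep the point minor.

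**Stronger readings that the protocol does not support:**

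- *Age belongs in the excess.* Age is not an allocation factor. Leaving it out may cost precision, but the ordinary standard error is correct in that respect.
- *Power rises from 80% to 84% at R² = 10%.* The balanced allocation already raises the group-only power to 81.3%, so the gain from adjustment is 84.0 − 81.3 = 2.7 points. At R² = 5% it is 82.0 − 80.6 = 1.4 points.
- *Attrition leaves the estimate biased.* Random loss restores some chance imbalance, which the ordinary standard error covers. The protocol gives no sign that loss will differ by group.

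**Conclusion.** The point holds in a limited, conditional form. C.2 balances the groups on three factors and the ANOVA stated in C.6 leaves them out. If the factors lead the sort and predict the outcome, the unadjusted standard errors are too large by about 0.5%, 2.6% or 5.4% for an assumed R² of 1%, 5% or 10%, and the tests are slightly conservative. The loss of power is 0.3, 1.4 or 2.7 points. The power figures also rest on the implied SD of 1.51, which assumes two-sided 5%, no multiplicity correction and 400 per group. The standard-error ratios do not depend on that SD.

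A reader might infer that the planned comparison is invalid or could yield false claims of effect. It is not and would not: the omission brings neither bias nor inflation of false positives. Severity is minor.

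**What to change.** - **C.6:** estimate the group contrasts from a linear model of the Wave 2 primary outcome on group plus race/ethnicity, geographic region and education, and apply the planned multiplicity adjustment to those contrasts.
- **C.2:** state that participants are sorted by the three factors first, with the random number ordering them within each cell. If the survey company in fact used another order, record that order; the adjusted model remains valid either way.
- **Optional:** age may be added for precision, but it is not part of this mismatch. Robust standard errors are not required by it.

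The cost is a sentence in each section. With five, four and four categories, as in the simulation, the factors use 4 + 3 + 3 = 10 parameters against 6 × 400 = 2400 expected Wave 2 respondents. The panel company already holds the variables. The protocol does not list what is transferred to the study team, so confirm that the three factors are in the de-identified file.

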**C.3. Eligibility Criteria**

- Inclusion criteria: 65 years; female; part of KnowledgePanel; able to complete survey in English.
- Exclusion criteria: personal history of breast cancer

KnowledgePanel already collects information on panel members' age, gender, English proficiency. We will independently include a screening question at the beginning of the survey regarding breast cancer history.

**C.4. Interventions and Choice of comparator:**

We will randomly assign women meeting eligibility to 6 groups (Table 1). The experimental groups 3-6 will read a message at Wave 1 that may be from either family/friend or the media followed by a second message from a clinician one to two weeks later at Wave 2, as research suggests that message decay occurs in 1-2 weeks. By presenting the non-clinician message first, we aim to mimic the real-world scenario where patients are often exposed to information from their family, friends and/or the media before a clinic visit.

The clinician message will be directed at reducing over-screening, mentioning the harms of over-screening and supporting screening cessation. We will systematically vary the non-

clinician message to be either consistent with the clinician message (also mentions harms of over-screening and supports screening cessation) or conflicting (mentions benefits of screening, supports continued screening and opposes screening cessation). We include a no-exposure control group (Group 1) where the participants read no message at either time point. We also include a single exposure group that reads only the clinician message (Group 2).

Table 1. Aim 2 experimental design

| Group # | Group type                | Wave 1        |                    | Wave 2     |                |
|---------|---------------------------|---------------|--------------------|------------|----------------|
|         |                           | Source        | Content            | Source     | Content        |
| 1       | Control (no exposure)     | No message    | No message         | No message | No message     |
| 2       | Control (single exposure) | Clinician     | Stop screening     | No message | No message     |
| 3       | Experimental              | Media         | Stop screening     | Clinician  | Stop screening |
| 4       | Experimental              | Family/Friend | Stop screening     | Clinician  | Stop screening |
| 5       | Experimental              | Media         | Continue screening | Clinician  | Stop screening |
| 6       | Experimental              | Family/Friend | Continue screening | Clinician  | Stop screening |

### C.5. Outcomes and timeline (Table 2):

Table 2. Aim 2 study outcomes and timing of assessments.

|             | Outcomes                                                                                       | Group 1 |    | Group 2 |    | Group 3/4 |    | Group 5/6 |    |
|-------------|------------------------------------------------------------------------------------------------|---------|----|---------|----|-----------|----|-----------|----|
|             |                                                                                                | W1      | W2 | W1      | W2 | W1        | W2 | W1        | W2 |
| Primary     | Support for screening cessation for hypothetical patient                                       | x       | x  | x       | x  | x         | x  | x         | x  |
| Secondary   | Screening intention for oneself                                                                | x       | x  | x       | x  | x         | x  | x         | x  |
| Secondary   | Screening attitudes                                                                            | x       | x  | x       | x  | x         | x  | x         | x  |
| Secondary   | Awareness of harms of screening                                                                | x       |    | x       |    | x         |    | x         |    |
| Secondary   | Negative perceptions of mammograms                                                             |         |    | x       |    | x         |    | x         |    |
| Secondary   | Perceived effects on making one think more carefully or seek more information about mammograms |         |    | x       |    | x         | x  | x         | x  |
| Secondary   | Emotional response                                                                             |         |    | x       |    | x         |    | x         |    |
| Exploratory | Outcomes related to conflicting messages (confusion, backlash, ambivalence)                    | x       |    |         |    |           | x  |           | x  |
| Exploratory | Open-ended impression                                                                          |         |    | x       |    | x         |    | x         |    |

Support for screening cessation for hypothetical patient: “How strongly do you believe that older women with a lot of health problems like [name] should get a mammogram in the next two years? Measured on a 7-point scale (1=definitely should get a mammogram; 7= definitely should not get a mammogram).

Screening intention for oneself: “How likely is it that you will get a mammogram in the next two years?” Measured on a 7-point scale (1=very likely to get a mammogram, 7=very unlikely to get a mammogram).

Attitudes:

- “For you, would you say getting a mammogram in the next two years is... 1=unimportant; 5=important; 1=harmful; 5=beneficial; 1=not worthwhile; 5=worthwhile;

- “For older women with a lot of health problems like [name], would you say getting a mammogram in the next two years is... 1=unimportant; 5=important; 1=harmful; 5=beneficial; 1=not worthwhile; 5=worthwhile;

Awareness of harms of screening: “Have you ever heard or read the following information? You could have heard or read this information during this survey or previously.” (Yes/No)

- For some women over age 65 who have a lot of health problems, medical guidelines recommend against regular mammograms.
- Mammograms can find slow-growing breast cancers that might never cause problems but can lead to unnecessary, risky treatments such as surgery or radiation.
- Mammograms can have false alarm results that may cause stress, anxiety, and require breast biopsy.

Negative perceptions of mammograms:

“Thinking about the information that was shared, please rate how much you agree or disagree with the following statement.” (1=strongly disagree; 5=strongly agree)

- This information discourages me from wanting to get a mammogram.
- This information makes getting a mammogram seem unpleasant to me.
- This information makes me concerned about the health effects of getting a mammogram.

Effect perceptions:

“Thinking about the information that was shared, please rate how much you agree or disagree with the following statement.” (1=strongly disagree; 5=strongly agree)

- This information would make me think carefully about getting a mammogram
- This information would make me want to find out more information about the potential benefits of getting a mammogram.
- This information would make me want to find out more information about the potential downsides of getting a mammogram.

Emotional response:

“The next question includes words that describe different feelings and emotions. Please indicate how you feel after reading the information that was shared”. (1=not at all; 5=extremely)

- Annoyed
- Interested
- Worried
- Reassured

Outcomes related to conflicting messages:

“Please rate how much you agree or disagree with the following statement.” (1=strongly disagree; 5=strongly agree)

- I find mammogram screening recommendations to be confusing.
- It is clear to me whether I should continue or stop getting mammograms.
- Medical guidelines provide good advice about mammogram screening.
- I trust my doctors’ advice about whether I should continue or stop getting mammograms.
- I have mixed feelings about getting mammograms.

Open-ended impressions: “We are now interested in what you were thinking about when you read the information that was shared. Please use the text box below to record your thoughts and ideas. Don’t worry about spelling and grammar. Please be completely honest and list all of the thoughts that you had.”

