|-----------------------|------------------------------------------------------------------------------------------------------------------------------------------------------------------------------------------------------------------------------------------------------------------------------------------------------------------------------------------------------------------------------------------------------------------------------------------------------------------------------------------------------------------------------------------|
|                       | Group 3 – message from news story at Wave 1 on screening cessation; message from clinician at Wave 2 on screening cessation.
Group 4 – message from family member at Wave 1 on screening cessation; message from clinician at Wave 2 on screening cessation.
Group 5 – message from news story at Wave 1 on screening continuation; message from clinician at Wave 2 on screening cessation.
Group 6 – message from family member at Wave 1 on screening continuation; message from clinician at Wave 2 on screening cessation. |
| Outcome measures      | Primary outcomes: support for stopping screening for a hypothetical older woman in the survey vignette
Secondary or other pre-specified outcomes: screening intention for participants; breast cancer screening attitudes; perceived message effectiveness; emotional response; negative perceptions of mammograms; awareness of screening harms; confusion or backlash about conflicting messages                                                                                                                                    |
| Eligibility           | Inclusion criteria: 65 years; female; part of an online survey panel called KnowledgePanel; able to complete survey in English.
Exclusion criteria: personal history of breast cancer                                                                                                                                                                                                                                                                                                                                                 |

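### The confusion, backlash and ambivalence items support only a conflicting-versus-consistent comparison: they have no same-wave no-exposure control and no clinician-only control

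*Protocol*

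**What the plan says.** Section C.4 sets up two controls. For the first: "We include a no-exposure control group (Group 1) where the participants read no message at either time point". For the second: "We also include a single exposure group that reads only the clinician message (Group 2"). Table 1 gives Groups 3 to 6 a media or family/friend message at Wave 1 and the clinician's stop message at Wave 2. In Groups 3/4 the Wave 1 message agrees with the clinician's; in Groups 5/6 it opposes it.

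Table 2 in section C.5 has an exploratory row, "Outcomes related to conflicting messages (confusion, backlash, ambivalence"). It is marked for Group 1 at W1, for Groups 3/4 and 5/6 at W2, and for Group 2 at neither wave. The registration summary in section A also names "confusion or backlash about conflicting messages" under its combined heading for secondary and other pre-specified outcomes.

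The five items are agreement statements on a 5-point scale, for example "I find mammogram screening recommendations to be confusing". None of them mentions a message that the respondent has just read.

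In section C.6 the aim for the main analysis is this: "The primary goal is to compare the experimental groups (Groups 3-6) at Wave 2 with both control groups". That sentence concerns the primary outcome, which Table 2 schedules in every group at both waves.

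**The concern.** The two controls are in the design so that the effect of a pair of messages can be set against no message and against the clinician message alone. For confusion, backlash and ambivalence neither reference is available at Wave 2: Group 1 answers at a different wave, and Group 2 does not answer at all.

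Conflicting messages are the subject of Aim 2, and these items are the direct measure of their possible harm. Suppose Groups 5/6 report more confusion than Groups 3/4. A reader will want to know whether the opposing message caused confusion or the agreeing message relieved it. A reader will also ask whether a lone stop message from a clinician is itself confusing. Both answers bear on which messages go forward to Aim 3, and the schedule can supply neither.

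**Working it through.** **The plan's own figures.** Section C.6 takes 400 per group at Wave 2 and 20% attrition: 400 / (1 − 0.20) = 500 per group at Wave 1, and 6 × 500 = 3000. Both reproduce. The 80% power for 0.30 points cannot be checked, because neither the SD nor alpha is given, but it is not needed here.

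**The schedule, cell by cell (Tables 1 and 2).**

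| Group | Wave 1 message | Wave 2 message | Conflict items at W1 | Conflict items at W2 |
|---|---|---|---|---|
| 1 | none | none | yes | no |
| 2 | clinician, stop | none | no | no |
| 3/4 | media or family/friend, stop | clinician, stop | no | yes |
| 5/6 | media or family/friend, continue | clinician, stop | no | yes |

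**What can be estimated.** Groups 5/6 and 3/4 are randomised and answer at the same wave. They are matched on source, number of messages and final clinician message, and differ only in the direction of the first message. The minimum detectable standardised difference at 80% power, two-sided 0.05, is (1.960 + 0.842) × √(1/n₁ + 1/n₂):

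- Groups 5+6 against 3+4, 800 v 800: 2.802 × √(2/800) = 0.14 SD.
- Within one source (5 v 3 or 6 v 4), 400 v 400: 2.802 × √(2/400) = 0.20 SD.

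The protocol gives no SD for these items. For an assumed item SD of 0.8 to 1.3, the first figure is 0.11 to 0.18 points and the second 0.16 to 0.26 points.

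**What cannot be estimated.** Let m(g, w) be the mean of group g at wave w. The available contrast is

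m(5/6, W2) − m(3/4, W2) = [m(5/6, W2) − m(1, W2)] − [m(3/4, W2) − m(1, W2)].

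The first bracket is the effect of a conflicting pair against no exposure, the second that of a consistent pair. The term m(1, W2) cancels and is never observed, so any difference is compatible with the first bracket carrying all of it, the second carrying all of it, or any split. With Group 2 the case is simpler: there is no value to compare with.

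**Using Group 1 at Wave 1 instead.**

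m(5/6, W2) − m(1, W1) = [m(5/6, W2) − m(1, W2)] + [m(1, W2) − m(1, W1)].

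The last bracket is the change from occasion and from having already taken one survey on the topic. It cannot be estimated, because Group 1 does not answer at Wave 2.

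If all 500 Wave 1 respondents in Group 1 are used, attrition adds a further term. Let returners have mean C and dropouts C − D. The full mean is 0.8C + 0.2(C − D) = C − 0.2D, so the contrast shifts by 0.2 × D. For assumed D of 0.1, 0.25, 0.5 and 1.0 points the shift is 0.02, 0.05, 0.10 and 0.20 points. Using only Group 1 women who return (about 400) removes this term but leaves the occasion and repeat-survey term.

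**With the items added at Wave 2.** Groups 5+6 against either control, 800 v 400: 2.802 × √(1/800 + 1/400) = 0.17 SD, or 0.14 to 0.22 points for an SD of 0.8 to 1.3.

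**The case against.** A reader might infer from Table 2 that the effect of conflict on these outcomes has no valid control at all. The documents do not support that. Groups 3/4 are a concurrent randomised comparator for Groups 5/6, and neither the clinician message, the wave nor the repeat survey can explain a difference between them. This part of the objection stands in full and fixes the limits of the point.

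Three further objections also stand:

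- Section C.6 promises the comparison with both controls for the primary outcome only, and its hypotheses concern support and intentions. Leaving Groups 1 and 2 out of the Wave 2 conflict items contradicts no stated analysis.
- Attrition is not inseparable from the message effect. Restricting Group 1 to Wave 2 returners deals with the loss of dropouts, and the choice may properly sit in an analysis plan that is not shown.
- A reader might infer that asking Group 1 these items at Wave 1 primes its later primary outcome. It is true that only Group 1 sees them then. But every group answers the awareness items at Wave 1, one of which says that guidelines advise against regular mammograms for some older women, and Groups 2 to 6 also read an explicit message. No material effect is shown, so this is no ground for the point.

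One more caution is fair: moving Group 1's items to Wave 2, rather than adding them there, would discard the only first-occasion measurement free of any message.

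None of this supplies the missing Wave 2 references. The items do not depend on having read a message, so nothing in their wording prevents asking Groups 1 and 2.

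**Conclusion.** The point holds in a limited form. For this exploratory item set, conflicting versus consistent messaging is validly estimable at Wave 2, with a detectable difference of about 0.14 SD. The schedule gives no same-wave no-exposure control and no clinician-only control. The trial therefore cannot tell whether conflict raises confusion or consistency lowers it, nor compare either with the clinician message alone.

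The detectable differences assume about 400 returners per group, two-sided 0.05 and no multiplicity adjustment; the values in points rest on an assumed item SD. The Wave 2 contrast also assumes that return does not depend on which Wave 1 message was read, an assumption that the primary outcome shares. The size of the occasion and repeat-survey effects is unknown.

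The weight is low to moderate. The outcomes are exploratory and no stated analysis fails, so this is a cheap improvement and not a flaw in the main comparison.

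**What to change.** In Table 2, mark the five conflict items at W2 for Groups 1 and 2 as well, placed after the primary outcome, so that all six groups answer at Wave 2. Group 1's W1 measurement may be kept as a message-free first-occasion value. If it is kept, Group 1's change between waves also estimates the occasion and repeat-survey effect among returners.

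If the items are not added, state that inference on these outcomes is limited to Groups 5/6 against 3/4, and that Group 1's W1 values are descriptive only.

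The cost is minor survey programming and about a minute of extra Wave 2 time in Groups 1 and 2, against the roughly 10 minutes that section D.2 expects. One limit remains: Group 2's clinician message will be one to two weeks old at Wave 2, whereas Groups 3 to 6 will have just read theirs. A comparison with Group 2 therefore does not equalise recency, and the primary outcome has the same limit.
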